#### Comparison Between Basic and Intensive Intervention

To explore the possible additional effect from intensive intervention, we will compare the intensive intervention to the basic intervention using similar models, regardless of whether the difference between the overall intervention group and control group is statistically significant. Considering the potential imbalance in the baseline characteristics between patients following the intensive intervention and those following the basic intervention, two propensity score methods will be applied. Both the propensity score adjusted regression based on a log-binomial model with GEE and the inverse probability of treatment weighting method will be used to evaluate the intervention effect [16,17] as the sensitivity to seek the consistency of the conclusion. The propensity score model will consist in a simple logistic regression with baseline covariates including age, sex, the baseline value of the analyzed outcome, education, duration of diabetes, comorbidities, economic development level, and locality (urban or rural). Baseline characteristics of participants will be described in a table separately before and after propensity score adjustments.

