### Intervention

Besides a standard training workshop for the contracted service providers (community, township, and county level doctors) in the intervention arm, the key components of intervention were one BP measurement and two blood glucose monitoring tests (at least one fasting blood glucose [FBG]) monthly, instruction for lifestyle change and medication accordingly, timely referral if an indicator is present, and quarterly performance review for the contracted service team. A mobile health–based information system, Graded ROADMAP, was developed and employed to support the contracted doctor team delivering the intervention. Another smartphone app, Your Doctor, was available for participants in the intervention arm to facilitate health education and communication between the designated doctors and patients. The use of Your Doctor depended on participants’ willingness and capability of using the smartphone app. At the end of this study, all the participants in the intervention arm were divided into two subgroups based on the actual use of Your Doctor: a basic intervention subgroup in which participants have logged in less than 4 times to the app throughout the 1-year follow-up and an intensive intervention subgroup in which the participants have at least 4 log-ins within 1 year.

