### Patient Characteristics and Baseline Comparison

Discrete baseline variables will be summarized by frequencies and percentages. Percentages will be calculated using the number of patients for whom data is available. Continuous variables will be summarized by using mean and SD, and median and interquartile range (Q1-Q3). No adjustment for clustering will be applied when comparing baseline characteristics. Standardized differences between groups in baseline characteristics will be reported. A less than 0.1 standard difference will be used to indicate a negligible difference in the mean or proportion of a baseline variable between treatment groups [14].

Variables for baseline measures will be tabulated, including demographic (age, sex, ethnicity), socioeconomic status (education level, household income, health insurance), anthropometric measurements (weight, BMI, waist circumference, BP), smoking status, diabetic complications, laboratory data (HbA_1c_, FBG, LDL-C, serum creatinine), and score of the summary of diabetes self-care activities.

Cluster characteristics will be summarized in stratified and overall randomization groups. The cluster characteristics at baseline are age of the community or village doctors, smartphone operation system (iOS or Android) that the community or village doctors were using, and number of patients with T2D registered.

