### Analysis of the Primary Outcome

#### Primary Analyses

The primary endpoint, control rate of HbA_1c_ at 1 year, will be first compared between all intervention groups and all control groups. The primary analysis of the intervention effect will be conducted using a log-binomial regression with generalized estimating equations (GEE) to account for clustering within communities and with adjustment for baseline HbA_1c_ as a continuous covariate (model 1). The raw number and percentage of patients with adequate control of HbA_1c_ at 1 year will be reported. The effect of the intervention will be presented as the relative risk (RR) of the proportion of HbA_1c_ levels <7% along with its 95% CI and corresponding *P* value. In cases of a convergence issue, the logistic regression with GEE and the Poisson regression with GEE will be both used as the alternative methods, with the Poisson regression as the sensitivity analysis. The odds ratio along with the indirectly derived RR will be reported for the logistic regression.

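### The self-selected intensive-versus-basic comparison leads with models built for a randomised contrast, and its one propensity score leaves out the community and several collected variables, so confounding could be read as an app effect

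*SAP article*

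**What the plan says.** All references are to the SAP article.

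- *Intervention*: app use was left to the patient, and at the end of the study "all the participants in the intervention arm were divided into two subgroups based on the actual use of Your Doctor". *Exposure to Intensive Intervention* sets the cut at four log-ins over the year.
- *Comparison Between Basic and Intensive Intervention*: "we will compare the intensive intervention to the basic intervention using similar models".
- *Primary Analyses*: the model being echoed is a log-binomial GEE "with adjustment for baseline HbA_1c_ as a continuous covariate (model 1"). *Covariates-Adjusted Analyses* (model 2) adds economic level, locality and any baseline variable that differs between intervention and control at P<.01.
- *Comparison Between Basic and Intensive Intervention*: the plan foresees baseline imbalance. It therefore adds propensity-adjusted regression and inverse probability weighting, which "will be used to evaluate the intervention effect [16,17] as the sensitivity to seek the consistency of the conclusion".
- Same section: both methods share one score: "The propensity score model will consist in a simple logistic regression with baseline covariates including age, sex, the baseline value of the analyzed outcome". The other named covariates are education, diabetes duration, comorbidities, economic level and locality. A table is to show patients' baseline data before and after adjustment.
- *Patient Characteristics and Baseline Comparison* lists household income, health insurance, BMI, smoking and the self-care score among the baseline measures. It adds cluster data: "The cluster characteristics at baseline are age of the community or village doctors, smartphone operation system" and number of registered patients. *Other Variables* shows that baseline insulin and oral drug use are recorded.

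**The concern.** Randomisation does not protect this contrast. Patients who keep opening a diabetes app may already be more motivated, better off or better served by their community team, and each of these could also improve HbA1c control. The plan recognises the imbalance, but as written it makes the remedy a check on the lead model rather than the lead itself.

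The remedy is also incomplete. The self-care score is the closest collected proxy for motivation, yet it is not in the named list. No term represents the community, although the imputation model in *Imputed Data Analyses* carries a cluster indicator. GEE clustering is there to give valid standard errors. It is not designed to balance community quality between users and non-users. Because both propensity methods use the same score, they share its omissions, and their agreement would say nothing about them.

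At stake is the claim that the app adds benefit beyond the basic service. The plan words this as an effect, gives it its own power statement, and attaches no caveat on residual confounding.

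**Working it through.** **Inputs.** From *Sample Size*: ICC 0.15; 40% control rate in usual care; 5-point target for both comparisons; 576 intervention communities; 19 patients per community at 1 year; 9-10 per community in each subgroup; stated power 89% (primary) and 93% (intensive versus basic). The rate in the basic subgroup is not given. I assume 45% (40% plus the 5-point target), against 50% with intensive use.

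**The plan's own figures reproduce.** The design effect is 1 + (m − 1) × 0.15.
- Primary: m = 19 gives 3.70; effective sizes are 288 × 19/3.70 = 1,479 and 576 × 19/3.70 = 2,958; power for 40% versus 45% is 88.8% (89.0% with unpooled variance).
- Intensive versus basic: m = 9 gives 2.20 and 576 × 9/2.20 = 2,356 per subgroup, power 93.0%; m = 10 gives 2.35 and 2,451, power 93.9%.

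The inputs are therefore read correctly. Power says nothing about bias, but it does mean that a spurious difference near 5 points would probably be statistically significant.

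**Scale of community confounding.** Between-community SD = √(0.15 × 0.45 × 0.55) = 0.193, and 0.05/0.193 = 0.26 SD. With a 40% base rate, √(0.15 × 0.40 × 0.60) = 0.190, again 0.26 SD.

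**Scale of patient-level confounding.** RR = 50/45 = 1.111, so the E-value is 1.111 + √(1.111 × 0.111) = 1.46. That is a minimum. For an omitted binary confounder with outcome ratio r and prevalence a in users and b in non-users, the spurious RR is [1 + a(r − 1)]/[1 + b(r − 1)]:
- r = 1.2, 60% versus 40%: 1.12/1.08 = 1.04, or +1.7 points on 45%.
- r = 1.46, 50% versus 34.2%: 1.23/1.158 = 1.06, or +2.8 points.
- r = 1.3, 70% versus 30%: 1.21/1.09 = 1.11, or +5.0 points.

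**Simulation under no app effect (assumed strengths).** There were 576 communities of 19, about half of patients were users, and the latent ICC was 0.15 for both app use and control. The score held one measured covariate but neither the community nor one patient-level driver. The driver's strength is a log odds ratio per SD on both app use and control. IPTW used 60 runs per row; the propensity-adjusted GEE (Poisson, exchangeable correlation) used 15.

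| Community correlation of app use and control | Driver | IPTW RR (points) | GEE RR |
|---|---|---|---|
| 0 | 0 | 0.998 (−0.1) | 1.007 |
| 0 | 0.3 | 1.035 (+1.6) | 1.038 |
| 0.3 | 0 | 1.077 (+3.3) | 1.027 |
| 0.3 | 0.3 | 1.110 (+4.8) | 1.061 |
| 0.5 | 0 | 1.128 (+5.5) | 1.045 |
| 0.5 | 0.3 | 1.162 (+6.8) | 1.083 |

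Adding the patient driver to the score but still no community left the IPTW RR at about 1.07 (correlation 0.3) and 1.12 (0.5). A within-community comparison that also included the driver was within 0.1 points of zero in every row. Patient variables and the community therefore both need handling. Exchangeable GEE removes part of the community confounding, not all.

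**The case against.** **Model 2 may be included.** A reader might infer that the lead comparison adjusts for the baseline outcome and nothing else. The text does not settle that: 'similar models' is plural and may cover model 2. If its selection rule were re-run for users versus non-users, income, smoking, BMI and the self-care score could enter. As written, however, the rule selects on intervention-versus-control differences, which do not target this confounding.

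**The wording is loose.** The sentence on sensitivity could mean that the two propensity methods check each other, and the word 'including' may leave the covariate list open. Both readings are possible. On either, the lead model or the score is not fixed, and two methods sharing one score still share its gaps.

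**A diagnostic is planned.** The before-and-after table could show residual imbalance in the listed patient variables. That stands, but the plan does not tie its 0.1 criterion to that table, does not list baseline drug treatment among the baseline measures, and states no consequence if balance fails.

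**The scale figures are generous.** They use the total between-community SD. Education, economic level, locality and baseline HbA1c would absorb some of it, so more than 0.26 SD would be needed. The ICC comes from hospital patients starting basal insulin, and the *Discussion* itself doubts that it transfers. *Sample Size* also plans on every community supplying 9-10 patients to each subgroup; an exactly even split would leave almost no between-community confounding. That is a planning average, though, and nothing in the design enforces it when patients choose. It also leaves patient-level confounding untouched.

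**Status.** The plan calls the comparison secondary and exploratory, and states openly that it is defined by actual use. That limits the weight of the point.

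**Conclusion.** The concern holds. As written, the plan leaves confounding by patient motivation and community quality that its lead models do not target and its propensity score does not name, and its consistency check could not detect it.

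The size is unknown. The 0.26 SD figure is a scale resting on an ICC of 0.15 and an assumed 45% rate; the simulated RRs rest on assumed correlations and driver strengths.

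Four stronger inferences are not supported:
- That confounding *would* produce an apparent app effect. The document gives no data on who logs in, so only *could* is justified.
- That a confounder of strength 1.46 *would* explain 50% versus 45%. It is the minimum that could; at 50% versus 34.2% prevalence it yields about 2.8 points.
- That the doctor's phone system drives patient log-ins. The patients' app is separate from the doctors' system, and no link is shown.
- That the trial's main result is affected. The randomised intervention-versus-control comparison is untouched.

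**What to change.** 1. Make one named propensity-based analysis the lead for this comparison, and state which models are supporting.
2. Close the covariate list and add self-care score, household income, insurance, smoking, BMI and baseline insulin and oral drug use.
3. Handle the community in the score by a random effect or by cluster-level covariates, such as community means, doctor age and number of registered patients. Alternatively, add a within-community (conditional or fixed-effect) outcome comparison as a supporting analysis. Avoid fixed community dummies together with doctor variables in a logistic score: the dummies make the doctor variables redundant, and communities with all or no users cause separation and extreme weights.
4. Apply the plan's 0.1 standardised-difference criterion after adjustment, including to the added variables.
5. Report the result as an association, with a sentence on residual confounding and, optionally, an E-value.

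The cost is SAP wording and extra terms from data already collected. The interval may widen, and communities with only users or only non-users would contribute little to a within-community comparison.

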### General Analysis Principles

Analyses will adjust for clustering at the village level. The intracluster correlation coefficients will be calculated and tabulated. The primary comparison will be made between the intervention population and the usual care population. As a secondary comparison, the effects of the intensive intervention (no less than 4 logins to the Your Doctor app in addition to the basic intervention) will be explored by estimating the effects of intensive intervention vs basic intervention. No formal interim analysis will be performed. The primary analysis will use all available data with no imputation. Imputation will be performed as a sensitivity analysis when missing observations in HbA_1c_ levels after 1 year exceed 10%.

Hypothesis tests will be 2-tailed with a 5% significance level maintained throughout the analyses. No adjustment will be applied for multiplicity, given that most of the effectiveness outcomes are correlated or consist in different versions of common variables. Outcomes will be presented in order of their priority (primary vs secondary), and only a limited number of subgroup analyses are prespecified. Subgroup analyses will be carried out irrespective of whether a significant treatment effect on the primary outcome is observed. Analyses will be performed in SAS, version 9.4 or later (SAS Institute).

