### Analysis of Secondary Outcomes

#### Analysis for Binary Categorical Outcomes

A similar analytic strategy as for the primary outcome will be followed for other binary outcomes. These include the proportion of FBG<7.0 mmol/L, BP<140/80 mmHg, and that of LDL-C<2.6 mmol/L, and the optimal control rate of combined ABC targets. A log-binomial regression with GEE and including baseline continuous values of the analyzed outcome variable as covariate (model 1) will be used. Other further adjusted analysis (model 2) and subgroup analysis will also be conducted, and the imputed analysis as well, if applicable.

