**Secondary outcomes**						
	FBG^d^ < 7.0 mmol/L		xxx (xx.x)	xxx (xx.x)	x.xx (x.xx-x.xx)	.xx
	BP^e^ < 140/80 mmHg^f^		xxx (xx.x)	xxx (xx.x)	x.xx (x.xx-x.xx)	.xx
	LDL-C^g^ < 2.6 mmol/L		xxx (xx.x)	xxx (xx.x)	x.xx (x.xx-x.xx)	.xx
	Composite diabetes control^h,i^		xxx (xx.x)	xxx (xx.x)	x.xx (x.xx-x.xx)	.xx

^a^Primary model: log-binomial regression with generalized estimating equation (GEE) with adjustment of the baseline value of the analyzed outcome and clustering. The logistic regression with GEE will be employed as the alternative method in case of non-convergence, with indirectly derived relative risk reported.

^b^RR: relative risk.

^c^HbA_1c_: glycated hemoglobin.

^d^FBG: fasting blood glucose.

^e^BP: blood pressure.

^f^Only systolic blood pressure at baseline and clustering were adjusted in the primary model for BP control.

^g^LDL-C: low-density lipoprotein cholesterol.

^h^Composite diabetes control: defined as HbA_1c_ level <7.0%, BP <140/80 mmHg and LDL-C <2.6 mmol/L.

^i^No baseline variable was adjusted in the primary model for the composite diabetes control.

**Table 3 table3:** Estimated effects of intervention compared to control on the change from baseline of continuous outcomes.

Secondary continuous outcome		Control, mean (SD)	Intervention, mean (SD)	Primary model^a^	
				Mean differences (95% CI)	*P* value

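### Combined ABC has no defined baseline value in the intensive-versus-basic propensity score, and two of three possible readings leave confounding by baseline control

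*SAP article*

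**What the plan says.** Patients in the intervention arm are split by their own app use at four log-ins in the year. The Intervention section says "The use of Your Doctor depended on participants’ willingness and capability of using the smartphone app". General Analysis Principles ranks the contrast below the randomized one: "As a secondary comparison, the effects of the intensive intervention" are to be explored.

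Because baseline imbalance is expected, "two propensity score methods will be applied": a propensity-adjusted log-binomial GEE model and inverse probability of treatment weighting (IPTW). They serve as sensitivity analyses to see whether the conclusion is consistent. The logistic propensity model uses "baseline covariates including age, sex, the baseline value of the analyzed outcome, education, duration of diabetes, comorbidities", economic development level and locality. On balance, the plan says "Baseline characteristics of participants will be described in a table separately before and after propensity score adjustments".

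Three other places bear on combined ABC:

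- Analysis for Binary Categorical Outcomes names ABC and says "A similar analytic strategy as for the primary outcome will be followed for other binary outcomes", with a log-binomial GEE model "including baseline continuous values of the analyzed outcome variable as covariate (model 1) will be used".
- Table 2, footnote i, says "No baseline variable was adjusted in the primary model for the composite diabetes control".
- Imputed Data Analyses puts baseline HbA1c, FBG, BP and LDL-C all together in the imputation model.

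**The concern.** ABC control at 1 year is determined by three measures, and the strongest baseline predictors of it are the same three measures at entry. Patients choose whether to use the app, so those who do may differ at entry in exactly these levels. A propensity score removes that difference only if it contains the levels.

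The score takes its one disease level from the outcome being analysed. That works for HbA1c or LDL-C control. For ABC it points at nothing definite. The two places that speak of an ABC baseline covariate conflict, and neither speaks of the propensity model. The comparison is to use models similar to the primary one. If footnote i is followed, that model has no baseline adjustment for ABC, and the propensity step carries the whole burden.

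Both propensity methods rest on the same score. A covariate missing from it biases both alike, so their agreement is no evidence against this confounding.

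**Working it through.** **The plan's own figure.** The only number given for this comparison is 93% power for a 5-point gain in HbA1c control (Sample Size). Inputs: 576 clusters per group, m = 9-10 patients per cluster, ICC 0.15, two-sided 5%. Design effect = 1 + (m − 1) × 0.15, which is 2.20 at m = 9 and 2.35 at m = 10. Effective n per group = 576 × 9 / 2.20 = 2,356, or 576 × 10 / 2.35 = 2,451. Power is 93.5-94.3% for 40% vs 45% and 93.0-93.9% for 45% vs 50%. The figure reproduces, so the sizing is not in question. It concerns HbA1c, not ABC.

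**Possible readings for ABC.** The ABC score could hold (a) no ABC information, as footnote i would suggest; (b) yes/no ABC status at baseline; or (c) the three component levels, as the call for continuous values would suggest.

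**Simulation with a true app relative risk of 1.** The following are assumptions, not taken from the documents:

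- three standardized baseline levels with mutual correlation 0.1;
- targets met by 40%, 40% and 45%, giving ABC of about 9% (the 40% for HbA1c and the under-one-tenth for ABC agree with the plan);
- half the patients are intensive users, as in the plan's sizing;
- baseline-to-1-year correlation 0.4 or 0.6;
- logit P(intensive) = −b × (sum of the three levels), so a positive b means better-controlled patients use the app more.

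The score is fitted by logistic regression under each reading. The IPTW relative risk is the weighted ABC rate in users divided by that in non-users. With 400,000 patients and about 18,000 ABC events per group, the standard error of log RR is about √(2 × 0.91 / 18,000) = 0.01.

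| b per SD | (a) no ABC information | (b) yes/no ABC | (c) three levels |
|---|---|---|---|
| 0 | 0.99 | 0.98-0.99 | 0.99 |
| 0.1 | 1.13-1.19 | 1.08-1.11 | 1.00-1.01 |
| 0.2 | 1.25-1.40 | 1.15-1.22 | 0.99 |
| 0.3 | 1.40-1.65 | 1.25-1.34 | 1.00 |

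The range in each cell runs over the two correlations. The row b = 0 is null within simulation error.

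A further run at b = 0.1-0.2 used both planned methods. It gave 1.16-1.34 under (a), 1.10-1.20 under (b) and 0.99-1.01 under (c), the same for IPTW and propensity-adjusted regression. With the sign of b reversed at 0.2, (a) gave 0.74 and (b) 0.83.

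**Outcomes whose own baseline is in the score.** HbA1c control with baseline HbA1c in the score gave 0.99-1.01, and LDL-C control gave about 1.00. BP and FBG control were not simulated.

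**How visible the imbalance would be.** For small b, the user-minus-non-user difference in each level is roughly b × (1 + 0.1 + 0.1) = 1.2b SD in size. That is 0.12 SD at b = 0.1 and 0.24 SD at b = 0.2. Both exceed the 0.1 standardized difference that Patient Characteristics and Baseline Comparison treats as negligible.

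**The case against.** A reader might infer that the ABC score certainly contains no HbA1c, BP or LDL-C level and so will show an app effect that does not exist. The documents do not support that. Footnote i describes the primary model for the randomized contrast, not the propensity model. The text on binary outcomes lists ABC among those given continuous baseline values, so reading (c) is open. The covariate list is introduced as including certain items and may not be closed. Its comorbidities may pick up diagnoses of hypertension or dyslipidemia, though not levels. The propensity comparison is described under the primary outcome and reaches ABC only through a general clause.

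It can also be said that the before/after table would show the problem, that nothing in the plan says app users start better or worse, and that the comparison is exploratory.

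Most of this stands, and it limits the point. What remains is that a plan written to fix methods in advance leaves the ABC baseline value open, and two of the three readings are biased under selection on control. The balance table could expose residual imbalance if it lists these levels, but the section attaches no limit or action to it. An outcome-specific score is not an error in itself.

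**Conclusion.** The point holds in a limited form. The baseline value for combined ABC in the propensity model is undefined, and the two statements about an ABC baseline covariate disagree. If the score lacks the component levels and app use is related to baseline control, the ABC contrast is confounded. At 0.1-0.2 log-odds per SD the false relative risk is about 1.10-1.34 when users start better; at a baseline-to-1-year correlation of 0.4 or 0.6 the range is 1.08-1.40. When users start worse it is 0.74-0.83 at 0.2. With the component levels in the score it is 0.99-1.01.

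Size and direction rest on the assumed selection, on equal selection for all three levels, and on a model without clustering or the other listed covariates. If app use is unrelated to baseline control there is no bias. The HbA1c outcome and the randomized comparison are not affected in this way. This is a worthwhile correction to a secondary, exploratory analysis and does not threaten the trial's main result.

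**What to change.** 1. Fit one propensity model for all intensive-versus-basic outcomes. In place of the outcome-dependent item, include baseline HbA1c, FBG, SBP, DBP and LDL-C as continuous variables, and keep the covariates already listed.
2. Show these five levels in the before/after table and judge balance by the 0.1 standardized difference the plan already uses for baseline comparisons.
3. Reconcile Analysis for Binary Categorical Outcomes with Table 2, footnote i, on the ABC baseline covariate, and state that the propensity comparison applies to ABC if that is intended.

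The cost is wording. All five measures are already on the plan's list of baseline variables, and one score replaces several. The one downside is that only sex, age and HbA1c must be present at baseline for the ITT population, so patients missing a baseline BP, FBG or LDL-C value need a simple, stated handling in the score.
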